## Methods and design

### Overview of study design

To achieve our goals, we are conducting a randomized, type III hybrid effectiveness-implementation study using a stepped-wedge design to compare passive implementation or “implementation as usual” to facilitation as the primary implementation strategy [23, 24]. We selected facilitation as the primary implementation strategy because each EBP is multi-component and none have fully been used before in the VA, potentially necessitating a higher-intensity and flexible strategy [25, 26]. However, given the anticipated spread of the AFHS model in the VA, we decided to contrast this strategy with implementation “as usual,” which is less intensive and costly and more aligned with IHI’s model. The SAGE QUERI was designed for internal VA operational proposes. In January 2019, all planned procedures were determined by the VISN Chief Medical Officer to be operations activities not constituting research and proceeded as such under VISN authority and oversight without IRB review according to the provision of VHA Program Guide 1200.21.

Our primary effectiveness outcome is “facility-free days,” generally defined as days alive and outside a hospital or nursing home [27–29]. Our primary implementation outcome is Reach, defined as how many eligible Veterans receive each intervention. Unlike typical cluster trials that assign clusters of sites to a control/comparison condition or an active treatment condition, all sites in a stepped wedge design eventually receive the active treatment condition after receiving the comparison condition for a scheduled period [23, 24]. This design is ethically indicated in circumstances when equipoise is insufficient to justify the use of a control condition for the entire study period (e.g., when the principle of justice precludes withholding an intervention proven beneficial). Clusters are randomized to start time for the more active implementation phase. As shown in the Additional file 1: Figure S1, we plan to use three “steps” with each including three VA medical centers and their associated clinics, randomizing each cluster to a different start time for Active Implementation.

### Description of interventions

We conducted a literature review of published interventions within each of the 4Ms to select an EBPs for implementation. We limited our search to interventions with either existing randomized, controlled trials, a strong evidence of clinical impact, and/or a history of successful prior implementation in the VA. We identified interventions that could be implemented in different care settings within each clinical site, as we hypothesized that asking a single care setting to initiate and support four different EBPs at once would not be feasible. Finally, we compared published interventions to existing VA priorities and programs with the help of VA national leaders to identify areas of alignment. As shown in Table 3, we selected four EBPs: Surgical Pause, EMPOWER (Eliminating Medications Through Patient Ownership of End Results), TAP (Tailored Activities Program), and CAPABLE (Community Aging in Place – Advancing Better Living for Elders).

**Table 3 Tab3:** Summary of age-friendly evidence-based practice interventions

	Surgical pause	Empower	TAP	CAPABLE
Description	“Surgical Pause” involves systematic screening for frailty using the Risk Analysis Index (RAI) prior to surgery, triggering care pathways that clarify goals pre-operatively	“Eliminating Medications through Patient Ownership of End Results” (EMPOWER) is a direct-to-consumer booklet sent to older adults receiving a high-risk medication on a chronic basis paired with academic detailing for prescribers	“Tailored Activities Program” (TAP) is a 4-month structured, manualized intervention led by an occupational therapist (OT) that trains caregivers of patients with dementia to deliver activities tailored to the care recipients’ interests and capabilities	“Community Aging in Place – Advancing Better Living for Elders” (CAPABLE) utilizes a nurse, occupational therapist, and handyperson to identify and facilitate the functional goals related to aging in place of low-income older adults with 1 ADL or 2 IADL impairments
Core components	• Prior to surgical decision making, patient completes the RAI • Patients with RAI ≥ 37 referred for goal clarification conversation • Clinician(s) and patient review treatment plan, with or without surgery, to align with patient’s overarching goals and values	• Identifying patient panel • Mail EMPOWER brochure which includes a self-assessment of risks for medication, presentation of evidence of harms, medication education, and suggestions for conversation with provider • Provider prescriber education	• OT formal training • OT conducts home assessment to identify Veterans’ preserved capabilities and interests • OT develops 3 tailored activity prescriptions • Caregiver and Veteran participate in at least 3 TAP sessions	• OT and nurse formal training • Staffing components: • OT assess functional abilities, home accessibility, and safety then collaborates with Veteran to create up to 3 ADL/IDAL goals • Nurse—assesses medical status and develops 3 nursing goals • Handy Person—completes home modifications/repairs
Example adaptations	• Which staff screen • Strategy for communicating results to surgeon • In-person versus virtual training • Which clinician completes goal clarification conversation	• Format of brochure • Timing of brochure mailing and communication with prescriber • Which staff mail the brochure • Number of mailings	• Other health professionals (social worker, psychologist, RN) may also implement TAP with OT supervision • Location of session • Number of visits	• Referral source • Addressing more critical and expensive home repairs • Number of sessions conducted virtually vs in home after the initial assessment
Patient eligibility	• Age 65 + • RAI ≥ 37 • Considering “major surgery” as defined by a VASQIP-eligible CPT code	• Age 65 + • Community-dwelling (i.e., not residing in a nursing home) • Receiving a prescription for a targeted drug class for at least 90 of the last 120 days from a VA prescriber	• Age 65 + • Has a dementia diagnosis • Has an adult caregiver willing/able to participate • Can participate in at least two basic ADLs	• Age 65 + • Low income • At least 1 ADL or 2 IADL deficiencies • Able to ambulate around house independently with or without an assistive device
Potential setting	Preoperative clinics (e.g., surgery, anesthesia, primary care, medical subspecialties)	Primary care, mental health	Home care, home-based primary care, caregiver support program	Home care

*VASQIP* Veterans Affairs Surgical Quality Improvement Program, *CPT code* Current Procedural Terminology, *VA* Veterans Administration, *RN* registered nurse, *IADL* Instrumental Activities of Daily Living

Each EBP has a primary focus on one of the 4Ms, yet all incorporate multiple age-friendly domains. The Surgical Pause (What Matters) is a preoperative frailty screening program that triggers referral of frail patients for a structured goal clarification conversation to ensure surgical treatment aligns with patient priorities [30–32]. EMPOWER (Medications) is a direct-to-consumer intervention shown to more than triple the rate of discontinuation of high-risk medications among older adults [33–37]. TAP (Mentation) is a home-based intervention that reduces functional dependence, dementia-related symptoms, and caregiver burden [38–41]. CAPABLE (Mobility) is a multidisciplinary home-based intervention that provides nursing care, occupational therapy, and home adaptations for older adults with impairments in Instrumental and Activities of Daily Living [42–44]. These EBPs are not mandated or part of routine clinical care both in VA and non-VA settings, despite substantial evidentiary support.

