#### Audit and feedback

Audit and feedback will provide data on performance and help sites with Reach, Adoption, and measuring preliminary evidence of Effectiveness (i.e., through run or control charts; [57, 61]). We will employ our experience in quality improvement to conduct rapid implementation and evaluation cycles to iteratively improve implementation strategies, particularly early in the Active Implementation phase. For example, we can review the VA medical record to evaluate what proportion of older surgical patients underwent frailty screening; or identify VA pharmacy fills for older Veterans who received the EMPOWER intervention. This approach will help the implementation team at each site to have a timely understanding of how implementation is going and together with the external facilitator problem solve to overcome identified barriers.

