### Phase 5: Evaluation (12 months)

The study will conclude with the “Evaluation” phase. We will evaluate implementation using the RE-AIM framework as part of PRISM (Table 2), comparing Implementation as Usual to Active Implementation. We plan to start evaluation 6 months following the Consolidation phase at each site, to allow for 12 months for evaluation to provide longer-term information on Maintenance outcomes, a key gap in the literature [63, 64]. While our EBPs vary by specific clinical focus, location of intervention (e.g., clinic, home), personnel involved, and duration, they will all be part of a cohesive effort to shift care to be more consistent with an AFHS. Thus, we will examine each EBP in two ways. Across EBPs, we define our *primary implementation outcome* as Reach, since an AFHS is primarily defined by whether all older adults receive “Age-Friendly” care. Reach is defined as the proportion of Veterans eligible for each EBP that received that EBP during the implementation phase (Table 2). We will measure Reach aggregated to the cluster level across participating sites. We will also capture how frequently patients receive the first part of the intervention (i.e., screening or referral), but not the second part (i.e., full delivery of intervention). Our *primary effectiveness outcome* across EBPs is “facility-free days” or the number of days older Veterans remain alive and outside the hospital or nursing home (for post-acute or long-term care). We will evaluate this outcome among all Veterans eligible for at least one EBP as well as among EBP cohorts. Additionally, we will capture *secondary outco*mes specific to each EBP, using convergent mixed methods informed by the RE-AIM framework (Table 2). Maintenance will be measured across EBPs using our primary implementation outcome (Reach), analyzing whether the proportion of eligible Veterans enrolled in the EBPs is stable, improves, or declines by more than 10% at the time of Evaluation (1 year following Active Implementation).

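### Surgical Pause eligibility is the result of the EBP's own first step, so the Reach denominator and the facility-free-days cohort can change with study phase

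*Protocol article*

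**What the plan says.** In Table 3 (Description of interventions), the first core component of Surgical Pause is "Prior to surgical decision making, patient completes the RAI". Under the second, patients at 37 or above are "referred for goal clarification conversation". The same cut-off appears in the patient-eligibility row, beside age 65 or over and consideration for major surgery "as defined by a VASQIP-eligible CPT code". The text after the table says Surgical Pause "is a preoperative frailty screening program that triggers referral of frail patients". That section adds that the EBPs are not mandated or routine in VA or elsewhere, and the Discussion says the same of VISN 4.

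Phase 5: Evaluation gives the primary implementation outcome: "Reach is defined as the proportion of Veterans eligible for each EBP that received that EBP during the implementation phase". It counts screening or referral as the first part of an intervention. It sets the facility-free-days population as Veterans eligible for at least one EBP, plus each EBP's own cohort. Maintenance is judged by whether Reach holds steady, improves or drops by more than 10%. Under Quantitative evaluation, the treatment variable is binary, before versus after Active Implementation, for both primary outcomes.

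For TAP, the criterion "Has a dementia diagnosis" can be read from records, while "Has an adult caregiver willing/able to participate" and participation in two basic ADLs are of another kind. CAPABLE requires ADL or IADL deficits, low income and independent ambulation. EMPOWER eligibility rests on prescriptions and is not affected.

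**The concern.** A denominator for comparing phases should be found in the same way in each phase. For Surgical Pause it is not: whether a Veteran counts as eligible depends on a test that the programme itself introduces and that facilitation is meant to spread. Randomising the start times does not help, because the selection happens after assignment and moves with the treatment variable.

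Two things are at stake. First, Reach could miss the change that facilitation produces, since every Veteran known to be eligible has already been screened. Second, the group whose facility-free days are compared can differ in make-up between phases even if the EBP has no effect.

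**Working it through.** **Step 1: eligibility set beside delivery (Table 3).**

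| EBP | Found in records without the EBP | Depends on an EBP step |
|---|---|---|
| Surgical Pause | Age, procedure code | RAI of 37 or more: explicit, the RAI is the first core component |
| TAP | Age, dementia diagnosis | Caregiver and two-ADL criteria may need contact; no core component is said to establish them |
| CAPABLE | Age; low income is not tied to delivery | ADL/IADL criterion overlaps with the OT functional assessment, which is not said to be the eligibility check |
| EMPOWER | Prescription record | None |

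**Step 2: Reach.** Let N be surgical candidates, p the share truly at or above the cut-off, s the share screened, and c the share of identified Veterans who receive the conversation.

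- Reach among Veterans known to be eligible = Npsc / Nps = c. Screening coverage cancels.
- Reach among all truly eligible = Npsc / Np = s × c.

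The documents give no value for p, s or c, so all are assumed. With N = 1,000, p = 15% and c = 50%:

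- Before, s = 5%: 1,000 × 0.15 × 0.05 = 7.5 known eligible and 3.75 reached. Reach is 3.75/7.5 = 50%; among all 150 frail candidates it is 3.75/150 = 2.5%.
- After, s = 80%: 1,000 × 0.15 × 0.80 = 120 known eligible and 60 reached. Reach is 60/120 = 50%; among all 150 it is 60/150 = 40%.

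Other assumed values:

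| s before, after | c before, after | Reach, known eligible | Reach, all truly eligible |
|---|---|---|---|
| 10%, 80% | 50%, 50% | 50% vs 50% | 5% vs 40% |
| 20%, 60% | 50%, 50% | 50% vs 50% | 10% vs 30% |
| 10%, 80% | 60%, 50% | 60% vs 50% | 6% vs 40% |

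In the last row Reach falls while delivery to frail candidates rises more than sixfold. Maintenance behaves in the same way: if screening dropped from 80% back to 5% with c unchanged, Reach would stay at 50% while the true figure fell from 40% to 2.5%.

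**Step 3: facility-free days, assuming no true effect.** Suppose the frailest are identified first, so that the mean of the identified cohort rises linearly by d days between near-zero and full coverage. The spurious phase difference in the Surgical Pause cohort is d × (s after − s before).

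- 10% to 80%: 5 × 0.7 = 3.5, 10 × 0.7 = 7 and 20 × 0.7 = 14 days.
- 20% to 60%: 5 × 0.4 = 2, 10 × 0.4 = 4 and 20 × 0.4 = 8 days.

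In the pooled cohort, multiply by the Surgical Pause share. For the 7-day case, shares of 5%, 10% and 25% give 0.35, 0.70 and 1.75 days. Over the whole grid the range is 0.05 × 2 = 0.1 to 0.25 × 14 = 3.5 days.

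A different assumption reverses the sign: if newly identified frail Veterans form 10% of the later pooled cohort and average 20 fewer days, the shift is 0.10 × (−20) = −2 days.

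The yardsticks in the Power analysis are a detectable change of 1.7 days and a meaningful difference of 6 days. The 1.7 days serves only for scale. A Hussey-Hughes calculation (assumed two-sided 5% level) does not reproduce it: the printed spread figures give 0.06 to 0.12 days, and swapping them gives 0.81 to 1.56. That is a separate matter.

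**The case against.** The article says eligible Veterans, not Veterans known to be eligible from an RAI done in care, and it does not describe how eligibility is established in control periods. A full protocol could fix a record-based rule. Target population describes the surgical group by evaluation by a surgeon, and Audit and feedback speaks of checking "what proportion of older surgical patients underwent frailty screening", so unscreened patients can be counted. Phase 5 will also record receipt of the first part without the second. Part of this stands: the wider pools exist and make the remedy feasible. But Target population adds the Table 3 criteria on top, the audit passage concerns feedback to sites, and neither is made the Reach denominator. Counting screening separately does not alter either primary outcome. The eligibility rule that is printed includes the RAI.

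The adjusted models include comorbidity, dementia and the JEN frailty index. They would reduce a case-mix shift but not remove it, and the first analysis is unadjusted. Target sites says only five sites suit Surgical Pause, which dilutes any effect on the pooled cohort.

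A reader might infer that eligibility for TAP and CAPABLE also becomes known only by delivering the EBP. The article does not say so. Dementia diagnosis is in records, low income is not tied to delivery, and existing home-care or caregiver-support services may already know the caregiver and functional status. A reader might also infer that facility-free days must fall after Active Implementation. That direction is not established: within the Surgical Pause cohort everyone meets the cut-off in both phases, and the pooled comparators include Veterans with dementia, whose hospitalisation rate was 45% (Study context).

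**Conclusion.** The point holds for Surgical Pause on the article's own text. Eligibility is an outcome of the first core component, and that eligibility defines the population for both primary outcomes in a comparison across phases.

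For Reach, the loss of sensitivity follows whenever eligibility is read from the RAI done in care; the figures of 50% vs 50% against 2.5% vs 40% depend on assumed screening and conversation rates. For facility-free days there is exposure to selection bias whose sign and size cannot be settled from the document. The illustrations give 2 to 14 days in the Surgical Pause cohort and 0.1 to 3.5 days pooled, or −2 days pooled under the opposite assumption. None of these is an estimate. For TAP and CAPABLE the problem is possible where a criterion is learned through EBP contact, but it is not shown.

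**What to change.** For both primary outcomes, define the Surgical Pause analysis cohort and index date from records available identically in every phase: Veterans aged 65 or over evaluated for a VASQIP-eligible procedure. Date entry from the surgical evaluation rather than the operation, since Table 3 allows the reviewed plan to end without surgery. If a frail subset is wanted, use a record-based measure such as the JEN index that the models already include. Report RAI completion, RAI of 37 or more, and the goal conversation as successive numerator steps over that fixed denominator.

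Apply the same principle to TAP (65 or over with a dementia diagnosis) and to CAPABLE wherever a criterion is ascertained only through EBP contact. Clinical eligibility for receiving each EBP stays unchanged.

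The cost is a redefinition using data the plan already draws on, and lower absolute Reach, because some Veterans in the denominator would not meet the bedside criteria. In the Step 2 example, Reach over all 1,000 candidates would be 3.75/1,000 = 0.375% and 60/1,000 = 6%. The ratio of 16 is the same as for 2.5% and 40%, so the contrast between phases is kept. A JEN-defined subset would not coincide exactly with RAI of 37 or more.

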### Study context

This project is occurring in VISN 4, a demographically and geographically diverse region comprising 9 VA Medical Centers covering 83 counties in Pennsylvania and Delaware and parts of Ohio, West Virginia, New York, and New Jersey. In VISN 4, 62% of the approximately 275,000 enrolled Veterans who use the VA for care are 65 or older; in 2018, 16% of this cohort was hospitalized at least once and 7% entered a nursing home for long-term care. These rates vary significantly across VISN 4 Medical Centers (11–24% and 4–8%, respectively) and are much higher in specific vulnerable populations. For example, Veterans with dementia had a 45% hospitalization rate and 20% newly entered nursing homes in 2018. The baseline variation in these rates suggests a potential opportunity to improve care of older Veterans who wish to avoid the hospital and “age in place.” Notably, the VA Medical Centers in VISN 4 include larger urban academic hospital campuses which provide more complex care (e.g., Pittsburgh, Philadelphia) as well as many rural sites (e.g., Erie, Altoona). The diversity of populations in VISN 4 will provide insight into potentially unique contextual implementation differences.

### Target sites

All nine VA Medical Centers (VAMC) in VISN 4 and their associated outpatient clinics will be eligible to participate in the four EBPs to the degree appropriate for their site. For example, every site has pharmacists (which is critical to EMPOWER), and all nine VA Medical Centers have Home-Based Primary Care (HBPC) or home care agencies suitable for implementation of TAP and CAPABLE—but only five sites across VISN 4 perform intermediate or complex surgeries suitable for the Surgical Pause. For TAP, CAPABLE, and EMPOWER, we are randomizing at the VAMC-level, and for Surgical Pause, we are randomizing at the level of the surgical service line level to achieve balance between the 3 clusters regarding case volume, case complexity, and patient comorbidity. Each medical center can decide which EBPs to participate in, although we are encouraging medical centers to adopt all four, where applicable, adhering to the AFHS model.

### Target population

Veterans eligible for inclusion in SAGE must be age 65 or older, community-dwelling (not in a long-term nursing facility for more than 100 days prior to receiving an EBP), and either receiving a treatment targeted by one of our EBPs (e.g., prescribed a high-risk medication or evaluated by a surgeon in consideration for a possible surgical procedure) or have a risk factor targeted by one of our EBPs (e.g., diagnosis of dementia, or functional impairments that prevent completion of at least one Activities of Daily Living [ADL] and are low-income). Each EBP has additional eligibility criteria that mirror criteria from the trials supporting each EBP (Table 3). Exclusion criteria for all EBPs include current receipt of hospice or current residence in long-term nursing home care. In addition, Veterans with severe mental illness will be excluded from EMPOWER, and Veterans without a caregiver will be excluded from TAP.

### Partnership approach

#### Evaluation team

The SAGE evaluation team is multidisciplinary and composed of experts in implementation science, mixed methods research, health systems research, health economics, quality improvement, data management, nursing, medicine, surgery, geriatrics, social work, psychology, gerontology, occupational therapy, and hospital administration.

#### Operational partners

QUERI program centers are required to demonstrate substantial a priori operational support to enhance the likelihood of successful project completion. In the case of SAGE QUERI, our key partners include the VA national office of Geriatrics and Extended Care and the Geriatrics and Extended Care Data Analysis Center (GEC DAC), the VA national Surgical Office, and VISN 4 leadership including the Director and Chief Medical Officer, as well as individual VAMC Directors and Chiefs of Staff. SAGE QUERI will assemble a VISN-wide Veterans Community Advisory Board to engage Veterans in implementation and dissemination activities. Further, we have enlisted multiple advisors for the project to serve on a Technical Expert Panel, including representatives from the IHI, geriatrics leaders, and VA administrators. The evaluation team is independent of the operational partners while simultaneously receiving feedback and guidance on mutual goals regarding implementation of the four EBPs.

